## Abstract

**Background:**

To cope with the upcoming demographic change, economic efforts in the European Union are undertaken to promote activities in research and development of Ambient Assisted Living (AAL) solutions. As a result, a large variety of AAL products will be available in the next years. Only very few of these products are comprehensively evaluated regarding different aspects of quality of life in the target population. The aim of this study is to examine the effects of AAL on quality of life, health and technology acceptance of people at advanced age living in assisted living homes providing them the ModuLAAr Ambient Assisted Living system.

**Methods/Design:**

A treatment group of adults aged 60 years and older will be recruited within the participating assisted living homes. At baseline, the participating volunteers will report on quality of life, subjective health and sociodemographic conditions. After system installation, prospective follow-up (1, 4, 12 and 18 months) with additional reporting on technology acceptance and usability of the system will be conducted. Mixed methods data collection, linking quantitative data to interview-gathered qualitative data will be applied. Primary outcome measure will be the change in quality of life and subjective health across study duration.

**Discussion:**

As there is currently very little evidence that AAL solutions can contribute to improved health and the particular dimensions of quality of life in elderly persons, there is a need to assess these technologies and services more carefully. This field trial seeks to investigate the most relevant aspects connected to advanced information and communication technologies and their impact on daily life of residents in assisted living conditions.

**Trial registration:**

ClinicalTrials.gov: NCT02130102.

## Background

The demographic change in the next centuries was identified as one of the biggest challenges for our society and economy by the World Health Organisation (WHO). The WHO reported that in 2025 there will be more than 1.2 billion people aged 60 years and more in the world. In 2050 there will be about 2 billion elderly people. To cope with the challenges which arise with the number of elderly subjects, the WHO recommended structured political actions to enable healthy and active ageing which have to be undertaken by governments and international organisations [1].

The European Commission also declared that the ageing population will have major impact on the productivity and economic growth of its member states [2]. The amount of people aged 65 years or more will increase from 17.4% in 2010 to 29.5% in the year 2060 which could lead to a doubling of the ratio of dependent elderly (people aged 65 and above relative to those aged 15-64) [3]. This change will result in a reduced care giver availability who can provide assistance and care to old people [4,5]. To cope with these aspects, the European Commission initialized the Ambient Assisted Living Joint Program(AALJP) [6]. The assumption of this program is that some aspects of the upcoming challenges can be addressed by information and communication technologies (ICT). The most important aspect of this approach is that ICT can help elderly people to improve quality of life (QoL), increase health and live independent for a longer time in their familiar surroundings. The way the AALJP seeks to promote activities for research regarding these technologies is usually summarized as Ambient Assisted Living (AAL) solutions [6]. That kind of socio-technical solution usually provides a huge variety of technical products and services. It could reach from smart home technologies to sensor based activity and health monitoring, telemedicine and telecare as well as security and emergency call systems. This is why these solutions may have extensive positive effects on individuals, the society, and economic and medical stakeholders [7]. Within the European Research Framework Programs, the European Union and its member states have invested more than 1 billion Euros for research and innovation in the field of AAL and will continue within the research program Horizon 2020 [6,8].

In the last years, the technology driven research approach focused on developing those solutions. This is why AAL-associated products are usually evaluated according to their technical feasibility. The impact on the end-users health and QoL, the user acceptance of the solutions and the usability of product were not yet taken into account sufficiently [7]. Recent activities in funding programmes show that these aspects will be investigated in upcoming large scale pilot projects. One of these field trials is the ModuLAAr project [9] which is conducted in eastern Austria. This study will investigate how this provided module based AAL solution improves elderly’s QoL, subjective health, technology acceptance and end-user usability. This is the first large scale study in Austria which investigates the proposed effects of AAL in a long-term field trial. It will add important information to already existing outcomes of other projects and future testing regions of AAL systems regarding experiences and outcome parameters.

## Methods/Design

### Overview

ModuLAAr is a research project approved and funded by the benefit-program of the Austrian Research Promotion Agency (FFG) and the Austrian Federal Ministry of Transport, Innovation and Technology (BMVIT). The main objective of the project is to equip up to 50 flats with an AAL solution that will be adapted according to the individual needs of the residents in assisted living homes. Those already existing homes as well as new built ones will be considered for integration of the different AAL-modules. The new buildings are located in 3 and the existing homes in 6 municipalities. People living in assistive living homes provided by the Samariterbund Burgenland Rettung und Soziale Dienste GmbH may be considered for participation within the project.

### Study design

To establish a practical study design for the given framework of the whole project, a quasi-experimental longitudinal study with pre- and post-tests is conducted to evaluate the impact of the different AAL modules within the study population. For the study 50 persons aged 60 and older are recruited who will receive the module-based AAL solution. Those people are not necessarily dependent elderly, they live in the assisted living accommodations with an option to get support of service and nursing staff when needed or wanted. The effects of ModuLAAr are evaluated at 1-, 4, 12 and 18-months follow-ups by comparing the quantitative and qualitative results to the outcome of 2 baseline assessment points. An overview of the study design and the assessment points is provided in Figure 1. Beside the requirements of the project´s consortium members the heterogeneous combination of technical appliances, which are adapted according to the housing conditions of the participants, the creation of a control group is not appropriate to evaluate potential impacts on the study population of this specific project.

**Figure 1 F1:**
[figure not shown]
Study design and assessment points.

The study protocol was provided to the responsible Ethics Committee of the KRAGES Burgenländische Krankenanstalten Ges.m.b.H. who declared that for this research project it is not necessary to file an application for ethics approval. Furthermore, the Ethics Committee of the Medical University of Vienna was asked for application who responded that, according to the confirmation of the responsible ethics committee of the KRAGES, no further steps for ethics approval will have to be done. The participants´ approval will be obtained by informed consent which compiles with the Declaration of Helsinki [10].

At the beginning of the study, all eligible participants are provided with in-depth information about the study and asked to sign the informed consent form. The protocol was registered at clinicatrials.gov (Identifier: NCT02130102).

### Recruitment and eligibility

After consortiums’ decision about the participating assisted living home locations, the project is presented to the residents and - if residents want to - their relatives by one or more sessions called ‘Info Cafés’. Due to the circumstances that some assisted living homes are connected to a local nursing home, also the associated social service staff will be introduced to the project. During the project presentation, the involved persons have the opportunity to ask questions about the provided solutions and to critically reflect eventual occurring prejudices regarding the applied technologies and services.

The volunteers who declare that they are willing to take part in the study are screened for eligibility. This study aims to recruit up to 50 residents aged 60 years and above who meet the inclusion criteria.

Inclusion criteria:

1. Male or female residents of an assisted living home of the Samariterbund Burgenland Rettung und Soziale Dienste GmbH

2. Aged 60 years and older

3. Able to provide informed consent

4. Nursing level ≤ stage 4

Exclusion criteria:

1. Mini mental state examination score < 17 at baseline assessment point 1 (BA1)

2. Not able or unwilling to complete questionnaires

3. Relevant health threatening event during study which avoids further participation

4. Death of the resident

Those who meet the inclusion criteria are asked to subscribe the informed consent provided by the investigators to participate in the project.

### Study objectives

The study aims to evaluate the provided ambient assisted living solutions by measuring the changes in QoL, subjective health and technology acceptance. The primary objective of this study is to increase the domain specific QoL of the involved residents by this intervention, measured with a mixed-method approach which takes into account quantitative as well as quantitative information.

It is proposed to increase social integration due to the provided technical solutions which will have impact on interaction with other residents and relatives. Further objective of the study is to improve resident´s knowledge of the individual health status and thereby have positive effects on health behavior.

Furthermore the results shall identify the key facts how technology acceptance for AAL solutions can be enhanced and influenced.

### ModuLAAr system

The system is based on a flexible and scalable home server architecture named Homer Platform [11] developed by the AIT Austrian Institute of Technology GmbH. User interface are tablet computers with a pre-loaded software application. Furthermore, a software platform will be provided to share data between the residents and their relatives or social services.

To address the building conditions, the new built homes are equipped in construction phase with a cable bound infrastructure and a centralized installation of the server; already existing houses will be adapted with wireless technologies and decentralized installation of mini-computers.

The ModuLAAr system consists of technologies and services which are applied in four module-domains (Figure 2) which correlate with the health and QoL domains which shall be impacted [9]:

**Figure 2 F2:**
[figure not shown]
The ModuLAAr Ambient Assisted Living System.

1. Social Interaction

2. Comfort

3. Security

4. Healthcare

### Social interaction

To enhance social interaction with relatives and the service provider, a video telephone, pre-installed on the tablet computer, will be provided. Additionally, a photo sharing platform is integrated in the system that enables residents to review photos on the tablet computers. The data can be administered by the study participants (contacts for video telephone, photos), social service staff or relatives if access is granted by the resident.

### Comfort

Smart home technologies are installed in the new buildings to monitor and control windows, doors, stove and light conditions. The existing houses are equipped with wireless sensors that enable status monitoring of the windows and doors.

To enhance comfort, there are reminder functions which appear on the tablet computer when appropriate. Messages are generated if defined calendar entries, e.g. birthdays, appointments or other relevant actions (e.g. medicine intake) have to be accomplished. The reminder functions can be administered by the residents, service provider or relatives who have access for using the software platform.

This module also involves a meal ordering system which enables easy access to provided menus of the social service provider. This function is limited to the homes that are connected to a nursing home with meal compartment.

### Security

The bathroom surveillance system is based on the installed movement detectors and software algorithms that calculate if a relevant event (e.g. falls) could have been occurred and sends automatically an emergency call to the defined alarm partner. The residents have the opportunity to get an emergency call system for their home and for outdoor activities (a mobile emergency call system) to manually send an emergency message if needed.

The security module provides warning messages of household equipment (e.g. to keep an eye on an active stove) and status information of the applied smart home technologies (e.g. close the door before going to bed).

### Healthcare

Participants receive a healthcare package, which is based on NFC-gadgets (near field communication devices). The device to collect health related data is a smart-phone with a pre-loaded software application developed by the AIT. The connected gadgets are blood pressure monitors, weight scales and blood glucose meters. The software application also provides the possibility to report the actual health conditions (levels: good, average and bad).

If the participants want to share their collected health-related data (e.g. blood pressure) with relatives, care service provider or medical doctors, they have the possibility to use this telemedicine-function for monitoring of data-trends.

### Intervention

After baseline assessment (BA1 and BA2), the participants are provided with the different ModuLAAr modules based on their individual interests and housing conditions (e.g. also residents without diabetes are provided with blood glucose meter if wanted; old buildings are equipped with smart home monitoring technology – the ability to control windows or doors is not provided in already existing old buildings). The installed devices will remain in the homes until the projects’ end. After installation, extensive initial system training takes place in the home of the resident. Our aim is that the enrolled study participants have the opportunity to use the system for at least 12 months until the project ends. Within study duration, a follow-up training session after 2–4 months, depending on the individuals’ need for training, is planned. Depending on the point of time of recruitment there will be up to 4 assessment points where technology acceptance and usability will be reviewed. All questionnaires are completed in the course of individual interviews with the residents to address their individual deficiencies if necessary (e.g. the participant is not able to fill in the questionnaires due to cognitive limitations). After the project is completed, the tablet computer will remain property of the resident.

### Measurements

The study participants are evaluated at 6 points in time: baseline assessment at 4 months (BA1) and 1 month before installation (BA2), 1 month after installation (AP1), after 4 months (AP2), after 12 months (AP3) and if applicable after 18 months or otherwise on project ending (AP4). Not each measurement is used on every point in time. To identify developing trends before intervention the data related to subjective health and QoL between the two baseline assessments (BA1, BA2) are compared to the equal time span of the two assessments points after installation (AP1, AP2). Table 1 summarizes the planned measurements at several times (BA1, BA2, AP1, AP2, AP3, AP4) in the study population.

**Table 1 T1:** Questionnaires and qualitative assessment methods in ModuLAAr

	**BA1 (−4 months)**	**BA2 (−1 months)**	**AP1 (1 month)**	**AP2 (4 months)**	**AP3 (12 months)**	**AP4 (18 months)**
**Eligibilty screening**						
MMSE	●				●	
**Quality of life/subjective health**						
WHOQOL-BREF	●	●	●	●		●
WHOQOL-OLD	●	●	●	●		●
EQ5D-VAS	●	●	●	●		●
Qualitative Interview "Health and QOL"				●		
Focus groups "Health and QOL"						●
**Technology acceptance/usability**						
TAEG	●					
Usability			●		●	●
Qualitative interview "Technology Acceptance"				●		
Perceived system satisfaction				●		●
Technology estimates	●			●		
Focus groups "Technology Acceptance"						●
Frequency of Usage (technical analysis)						●
Visitation Protocols			●	●	●	●
Test calls and hotline contacts			●	●	●	●
**Other measurements**						
Sociodemographic Parameters	●					
Health threatening event in the past	●			●		●
Support for limitations	●			●		●

For evaluation of the outcomes a mixed-method approach with qualitative and quantitative methods is applied. Because of the heterogeneous combinations of technologies and participants, this modus operandi will provide the ability to gather additional information for qualitative analysis to the data collected for quantitative analysis.

Following measurements are performed:

Measurement for eligibility screening:

• MMSE: Cognitive function assessed by the German version [12] of the Mini Mental State Examination [13]

Measurements of health status and QOL:

• WHOQOL-BREF [14]: German version of the short form of the World Health Organization Quality of Life Questionnaire (Question nr. 21 was omitted due to the concerns of the consortium members)

• WHOQOL-OLD [15]: German version of the World Health Organization Quality of in the Elderly Questionnaire (Domains: “sensory”, “functions”, “autonomy”, “activities in the past, present and future”)

• EQ-5D VAS [16]: German Version of the Euroqol Visual Analogue Scale from the EQ-5D Quality of Life Questionnaire (The EQ-5D Questions 1–5 were omitted due to the concerns of the consortium members)

• Health and Quality of Life - Interviews: Semi-structured qualitative interviews and focus groups according to the bio-psycho-social model of Engel [17] and the multidimensional QOL-approach of the WHO [18]

Measurements of technology acceptance and usability:

• TAEG [19]: “Measuring technology affinity” questionnaire of the Technical University of Berlin.

• USABILITY Questionnaire developed by the usability competence team of the FH Technikum Wien based on: The System Usability Scale (SUS) [20], User Experience Questionnaire (UEQ) [21] and Microsoft Product Reaction Cards® [22]

• Technology acceptance - Interviews: Semi-structured qualitative interviews and focus groups according to the models of McCreadie&Tinker [23] for assistive technology for older people and the technology acceptance model(TAM) of Davis [24]:

• Perceived satisfaction question: “How many points you would give us for the ModuLAAr System?” (5-point Likert scale; AP2, AP4)

• Technology estimates:

What are your general estimates regarding the different modules (of the previous presentation)?” (open format, only at BA1)

“Which are the pros and cons you are estimating regarding the provided technologies?” (open format, only at BA1)

“Which estimates regarding the system had been met/had not been met?” (AP2, AP4)

• Frequency of system usage: The frequency how often the products had been used will be analyzed and reported anonymously (AP4)

• Visitation protocols: The visits will be documented in protocols that provide further input to relevant issues of the participants daily life and technology usage (AP3, AP4)

• Test calls and documentation of hotline contacts: Periodical phone calls are conducted by project staff to gather relevant information for issues arising with the provided technologies (AP1- AP4). Furthermore the participants’ hotline contacts are documented to identify for what reason the hotline was called (AP1- AP4).

Other Measurements:

• Socio-demographic parameters: sex, level of education, working experience, income, former housing conditions, chronic diseases, frequency of falls, previous health threatening events (BA1, AP2, AP4), level of social support, medicine intake.

• Support for limitations questions:

What are the most important physical limitations during the activities of daily living?” (open format)

“How important it is for you to get more support by doing your activities of daily living?” (5-point Likert scale)

“How important it is for you to get more support for your memory?” (5-point Likert scale)

“How secure do you feel in your environment/ flat?” (5-point Likert scale)

### Statistical analysis

Analyses will be conducted using SPSS® version 21.0 (SPSS Corp, Chicago, Illinois, USA) and Microsoft Excel 2010® software. Descriptive statistics and interferential statistics are performed. The sample data is carried out by frequencies or percentages, means, standard deviation, and graphics. Descriptive statistics are used to summarize demographic parameters and baseline data. General Linear Models (ANCOVA) controlling for baseline performance and other confounding variables is used if required. The delta-outcome of the baseline assessments (delta of BA1 to BA2) will be compared to the iterative delta of the data gathered by the intervention assessment (e.g. delta of AP1 to AP2, delta of AP1 to AP3) of each participant. To partially overcome the limitation of the lack of having a control group in the interim project analysis, the outcome data of the evaluated study population (delta of AP1 to AP2) is compared to those participants who finished the baseline assessment at that point in time (the same month) but are not yet provided with an installed system. All tests are two-sided at a significance level of p <0.05. T-test is used to compare baseline data and data of the follow-ups. Pearson and Spearman correlation coefficients are used for confounder identification. For the case that normal distributions couldn’t be reached non parametric tests (Wilcoxon, Mann-Whiteney-U-Test) are used in combination with Spearman and Kendall´s tau correlation coefficients.

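### The trend-controlled quality-of-life comparison leaves out the interval that contains installation, so a gain reached by month 1 and then sustained cancels out of it

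*Protocol article*

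**What the plan says.** The Measurements section places the visits as "baseline assessment at 4 months (BA1) and 1 month before installation (BA2), 1 month after installation (AP1), after 4 months (AP2"), with later visits at 12 and 18 months. To detect trends before the intervention, it says that the subjective-health and QoL data "between the two baseline assessments (BA1, BA2) are compared to the equal time span of the two assessments points after installation (AP1, AP2").

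The Statistical analysis section repeats the comparison: "The delta-outcome of the baseline assessments (delta of BA1 to BA2) will be compared to the iterative delta of the data gathered" after installation, with the examples "e.g. delta of AP1 to AP2, delta of AP1 to AP3) of each participant". For the interim analysis, "the outcome data of the evaluated study population (delta of AP1 to AP2) is compared to those participants who finished the baseline assessment" in the same month but have no system yet.

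Two other analyses are named: "T-test is used to compare baseline data and data of the follow-ups" and "General Linear Models (ANCOVA) controlling for baseline performance and other confounding variables is used if required".

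Table 1 schedules WHOQOL-BREF, WHOQOL-OLD and the EQ-5D VAS at BA1, BA2, AP1, AP2 and AP4, with nothing at AP3. The Abstract makes change in QoL and subjective health over the study the primary outcome.

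**The concern.** Each delta in the trend-controlled comparison lies wholly before or wholly after installation. The comparison therefore asks whether the slope after month 1 differs from the slope before installation. It does not ask whether residents moved to a different level once the system was in place.

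With no control arm, the second baseline and the residents still waiting for a system are the main quantitative safeguards against background trend. Both are used in a contrast that cannot register an early, lasting gain. The one named test that clearly spans installation leaves the trend uncorrected. On the text as written, the trial would have no trend-adjusted estimate of an effect that arrives in the first month.

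**Working it through.** **Inputs from the article.** Visit times BA1 = −4, BA2 = −1, AP1 = +1, AP2 = +4, AP4 = +18 months; up to 50 residents; two-sided 5% tests. The article gives no SD, within-person correlation or effect size, so those below are assumptions.

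**The plan's own figure.** The two spans are stated to be equal. BA2−BA1 = −1−(−4) = 3 months and AP2−AP1 = 4−1 = 3 months, so this is reproduced. The omitted interval BA2→AP1 is 1−(−1) = 2 months and contains month 0.

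**Expected value of the planned contrast**, C = (AP2−AP1) − (BA2−BA1), with background trend b points per month. The trend contributes 3b − 3b = 0, so only the effect's shape matters:
- Sustained step S by month 1: C = (S−S) − 0 = 0.
- Gain of 5 at month 1 fading to 3 at month 4: C = 3−5 = −2.
- Effect growing linearly to 5 at month 4 (1.25 at month 1): C = 5−1.25 = 3.75.

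In a simulation of the sustained step (n=50, 10,000 runs per setting, steps of 0.3 to 0.8 SD, correlations 0.5 to 0.8), the planned test rejected in 4.6% to 5.3% of runs, which is its type I error rate.

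**The uncorrected comparison.** AP2−BA2 spans 5 months and equals S + 5b. With S = 5 and an illustrative b = −0.5, it is 5 − 2.5 = 2.5.

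**Contrasts that span installation.** Variances are in units of σ²(1−ρ) per resident, under compound symmetry.
- *Level change under one common linear trend, four visits:* (4/3)(AP1−BA2) − (1/3)(AP2−BA1). Trend: (4/3)(2b) − (1/3)(8b) = 0. Step: (4/3)S − (1/3)S = S. Variance: 2(16/9) + 2(1/9) = 34/9 = 3.78. Adding AP4 lowers it to 1.44.
- *Simple delta:* (AP1−BA2) − (2/3)(BA2−BA1). It also returns S. Variance: 1 + 25/9 + 4/9 = 38/9 = 4.22.
- *Projection of the two-point pre-trend to month 4:* (AP2−BA2) − (5/3)(BA2−BA1). It also returns S. Variance: 1 + 64/9 + 25/9 = 98/9 = 10.89.
- *Planned contrast:* variance 4.

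**Precision, assuming n=50, SD 15, ρ=0.7.** The unit is 225 × 0.3 / 50 = 1.35.
- Planned contrast: SE √(4 × 1.35) = 2.32; power for a 5-point sustained step is 5%.
- Level change: SE √(3.78 × 1.35) = 2.26; power for 5 points about 58%.
- Simple delta: SE √(4.22 × 1.35) = 2.39.
- Projection to month 4: SE √(10.89 × 1.35) = 3.83; power about 25%.

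Over ρ = 0.5 to 0.8 the unit runs from 2.25 to 0.90, so the level-change SE runs from 2.92 to 1.84. The zero expectation of the planned contrast does not depend on ρ.

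**Limit of the level change.** For the linearly growing effect above, the four-visit level change is (4/3)(1.25) − (1/3)(5) = 0, while the planned contrast gives 3.75. The two contrasts answer different questions.

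**The case against.** The strongest reply is that the plan does look across installation. The t-test sets baseline against follow-up data, the Study design section evaluates effects against the two baselines, and the Discussion rests inference on change from baseline to post-test. The article never calls the delta comparison main or primary, gives its purpose as detecting trends before the intervention, and describes the study as explorative. All of this stands. A reader might infer that an early benefit would escape the whole analysis, or that the trial's principal contrast is blind to it. The documents support neither reading.

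Two further replies carry less weight. The deltas in the Statistical analysis section are introduced only as examples, but the Measurements section fixes AP1–AP2 for QoL and subjective health without that qualifier. AP1→AP3 cannot be formed for these outcomes because Table 1 has no QoL measure at AP3, and AP1→AP4 also starts after installation. The ANCOVA is conditional and adjusts for baseline performance and confounders; no pre-installation slope is named. Detail may have been left to an analysis plan that is not shown, but this contrast is stated, not omitted.

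**Conclusion.** The point holds for the trend-controlled comparison and for the interim comparison with residents not yet equipped. For a sustained step present by month 1, the expected contrast is exactly 0 under any linear background trend. For a gain that partly fades, the sign is reversed. Neither result needs an assumption about SD or correlation.

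What is missing is a trend-adjusted estimate that includes the step. The t-test supplies an unadjusted one, whose error at month 4 is five times the monthly trend. The SE and power figures rest on the assumed n=50, SD 15 and ρ=0.7 and are illustrative. Because the study is explorative and does not rank its analyses, this is a should-fix change to the analysis.

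**What to change.** Amend the Measurements and Statistical analysis sections so that the trend-adjusted analysis spans installation.

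- Fit a linear mixed model to all QoL visits (BA1, BA2, AP1, AP2, AP4) with a random resident intercept, a common linear time trend and an installed yes/no term. Name the level change as the trend-adjusted contrast.
- Add a slope-change term as a sensitivity analysis. On the first four visits its estimate is the planned contrast divided by 3, so the existing comparison is kept in that role.
- If a simpler calculation is preferred, use (AP1−BA2) − (2/3)(BA2−BA1).
- In the comparison with residents not yet equipped, start the installed residents' change at BA2 instead of AP1, and scale for the different span (2 months to AP1, against 3 months between the baselines).
- Do not make the projection of the two-point pre-trend to month 4 the main contrast; its variance is 10.89 against 3.78.

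The cost is wording and analysis time, with no new data. The price is an assumption: the level-change model takes one linear trend before and after installation, and the gain from adding AP4 relies on that trend holding to 18 months. An effect that builds up gradually shows mainly in the slope-change analysis, so both should be reported.

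### The plan names an AP1-to-AP3 change and a 12-month evaluation, but Table 1 schedules no quality-of-life or subjective-health scale at AP3, so neither can be computed for those outcomes

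*Protocol article*

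**What the plan says.** All references are to the protocol article.

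- **Abstract, Methods/Design.** The primary outcome is not tied to one visit: "Primary outcome measure will be the change in quality of life and subjective health across study duration".
- **Study design.** "The effects of ModuLAAr are evaluated at 1-, 4, 12 and 18-months follow-ups by comparing the quantitative and qualitative results", the comparator being the two baseline assessments.
- **Measurements.** AP3 is the visit "after 12 months (AP3"). AP4 takes place "if applicable after 18 months or otherwise on project ending (AP4"). The section cautions: "Not each measurement is used on every point in time". It also says that the quality-of-life and subjective-health change between the two baselines is compared with the change from AP1 to AP2, chosen because the spans are equal.
- **Table 1.** WHOQOL-BREF, WHOQOL-OLD and EQ-5D VAS are marked at BA1, BA2, AP1, AP2 and AP4. The AP3 cell is empty in all three rows. The quality-of-life interview is at AP2 only, and the corresponding focus groups are at AP4 only.
- **Statistical analysis.** "The delta-outcome of the baseline assessments (delta of BA1 to BA2) will be compared to the iterative delta" of the post-installation data, with two examples: "e.g. delta of AP1 to AP2, delta of AP1 to AP3) of each participant".
- **Intervention.** "Our aim is that the enrolled study participants have the opportunity to use the system for at least 12 months until the project ends".

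**The concern.** The analysis section names a change score that needs an AP3 value, and the schedule collects no AP3 value for the outcomes that the change scores are meant to describe. Anyone who follows Table 1 in the field will reach the analysis without the data for one of the two example comparisons, and a questionnaire not given at month 12 cannot be recovered later.

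The visit concerned also matters. The Intervention section aims for at least 12 months of use, so month 12 is the latest fixed-date visit that the design hopes every resident will reach. AP4 has no fixed date. As scheduled, everything the study learns about quality of life after month 4 comes from one visit whose timing differs between residents. A resident who leaves after month 12 but before AP4 has no quality-of-life score later than month 4.

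**Working it through.** No sample-size, power or alpha figure is involved. The check is whether the schedule supplies what each stated comparison needs.

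**Step 1. What the comparison needs.** Setting BA1-to-BA2 against AP1-to-AP3 within each participant needs the same measure at four visits: BA1, BA2, AP1 and AP3.

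**Step 2. What Table 1 supplies.** These are all the measures marked at AP3, with the three scales below them for contrast.

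| Measure | BA1 | BA2 | AP1 | AP2 | AP3 | AP4 |
|---|---|---|---|---|---|---|
| MMSE | yes | – | – | – | yes | – |
| Usability | – | – | yes | – | yes | yes |
| Visitation protocols | – | – | yes | yes | yes | yes |
| Test calls and hotline contacts | – | – | yes | yes | yes | yes |
| WHOQOL-BREF | yes | yes | yes | yes | – | yes |
| WHOQOL-OLD | yes | yes | yes | yes | – | yes |
| EQ-5D VAS | yes | yes | yes | yes | – | yes |

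**Step 3. Match the two**, over all rows of Table 1.

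- Measures at BA1, BA2, AP1 and AP2: 3 (the three scales).
- Measures at BA1, BA2, AP1 and AP4: the same 3.
- Measures at BA1, BA2, AP1 and AP3: 0.

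So the AP1-to-AP3 example cannot have been meant for some other outcome. Only the three scales are taken at both baselines, and none of them is taken at AP3. The 12-month evaluation in the Study design section fails for the same reason: no AP3 measure was also taken at both baselines. MMSE comes nearest, but it is missing at BA2 and is listed as eligibility screening.

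**Step 4. Spans**, from the nominal visit times −4, −1, 1, 4, 12 and 18 months.

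- BA1 to BA2: −1 − (−4) = 3 months
- AP1 to AP2: 4 − 1 = 3 months
- AP1 to AP3: 12 − 1 = 11 months
- AP1 to AP4: 18 − 1 = 17 months
- AP2 to AP4, the interval without these scales: 18 − 4 = 14 months

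The last figure is nominal. AP4 moves to project end for residents who do not reach 18 months. If such a resident has just the 12 months of use that the Intervention section aims for (an assumption, since this is an aim and not a guarantee), the interval is 12 − 4 = 8 months. The range is therefore about 8 to 14 months.

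**The case against.** **The schedule was never meant to be complete at every visit.** The Measurements section says so, and the AP1-to-AP3 change is only an example. Both facts explain why a cell may be blank. Neither supplies the data, and an example of a planned analysis should be one that can be run.

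**It may be a slip for AP4.** That is possible, and it would repair the Statistical analysis section. The 12-month claim in the Study design section would still conflict with Table 1.

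**It may be an artefact of a broken table.** The MMSE and usability rows carry marks in the AP3 column and the cell positions are consistent, so the blanks are genuine.

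**The main contrasts survive.** This stands. The equal-span comparison of BA1-to-BA2 with AP1-to-AP2 is fully supported, as is the interim comparison, which uses only AP1-to-AP2. AP4 gives a closing assessment with all three scales. The Discussion calls the study explorative and does not claim causal certainty.

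Four stronger readings are tempting, and the article does not support them:

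- *The primary outcome cannot be computed.* No separate 12-month primary outcome is defined. The outcome is change over the whole study, and it can be computed at AP1, AP2 and AP4.
- *No resident will have a score near month 12, and all have a 14-month gap.* A late recruit whose AP4 falls at project end may be assessed near month 12. None of the three scales is scheduled for AP3, which is a narrower statement.
- *A given number of 12-month values is lost through attrition.* The article gives no loss rate, so no count can be derived.
- *Month 12 should become the fixed primary time point.* That would be a redesign. The inconsistency can be resolved without it.

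**Conclusion.** The point holds as an internal contradiction between schedule and analysis. The AP1-to-AP3 comparison with the baseline change cannot be computed for any measure in Table 1, and no 12-month value of WHOQOL-BREF, WHOQOL-OLD or EQ-5D VAS is scheduled. One of the two example change scores and one of the four stated evaluation times are affected; the analyses at AP1, AP2 and AP4 are not.

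The practical consequence is that quality of life after month 4 rests on a single visit of variable date. The conclusion relies on Table 1 being the operative schedule and on AP3 meaning month 12, as the Measurements section defines it.

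**What to change.** Reconcile the Study design and Statistical analysis sections with Table 1 by one of two routes. Either resolves the contradiction.

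1. **Add the data.** Mark WHOQOL-BREF, WHOQOL-OLD and EQ-5D VAS at AP3. The assessment already exists and the questionnaires are already in use, so the cost is a schedule amendment and a longer interview. State that AP1-to-AP3 spans 11 months against 3 months for the baseline change, so it is not the equal-span comparison described under Measurements and should not be presented as one.
2. **Correct the text.** Replace AP1-to-AP3 with AP1-to-AP4 in the Statistical analysis section and remove the claim of quality-of-life evaluation at 12 months. This costs only wording, but long-term quality of life then continues to rest on AP4 with its varying date. The span problem also remains, nominally 17 months against 3, and should be stated.

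The first route is available only while AP3 assessments are still to come; for any already completed, only the second is left.
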